## Abstract

Contrary to North America and Europe, the prevalence of hypertension is rising in West Africa. With a transition from whole foods to processed foods in Nigeria, diet plays a key driver of hypertension. To combat this, the national nutritional guidelines in Nigeria were implemented, but their translation into actionable tools for clinicians remains a challenge. Currently, there are no simple dietary assessment tools that are concise and suitable to be incorporated into clinical care without requiring extensive data analysis while still providing personalised dietary support to their patients. This study aims to deliver a clinically tested and validated short dietary assessment tool for clinicians, patients, and researchers across Nigeria to provide personalised dietary advice for patients with hypertension. The study will be conducted in two phases: Phase 1 (n = 75) will investigate the feasibility of the short FFQ and its agreement with 24-hour dietary recalls (3x) in a clinical setting in Nigeria. During the analysis of Phase 1 data, a scoring system will be developed based on the associations between individual food items in the FFQ and measures of hypertension. Phase 2 (n = 50) will assess the acceptability of the FFQ and validate the association between the FFQ score and hypertension. **Expected outcomes:** The development of a clinically tested and validated short food frequency questionnaire that will be ready to use by clinicians, patients, and researchers across Nigeria to support the prevention and management of hypertension. This study will contribute to knowledge on dietary assessment and hypertension prevention by developing a validated and acceptable FFQ, which will be valuable for clinicians and researchers for personalised dietary recommendations to combat hypertension in Nigeria.

## Introduction

### Background

Hypertension, defined as sustained high blood pressure, is the leading preventable risk factor for cardiovascular disease and the number one cause of death globally [1]. Approximately 40% of people aged 30–79 years have hypertension, with two-thirds of cases living in low- and middle-income countries, including African countries [2, 3]. The most recent data from the World Health Organisation (WHO) show that the African region has the highest prevalence of hypertension (35.5%), with the Americas having the lowest (18%) [4]. 2. On the contrary, West African countries like Nigeria have shown a consistent increase in the prevalence of hypertension during this same time period. The most recent data estimate a 15.3% increase in hypertension rates in Nigeria from 2010 to 2019 [4–8], which has directly led to a documented increase in the prevalence of heart disease, stroke, and chronic kidney disease [9, 10].

The increase in hypertension rates in West African countries has been attributed to unhealthy dietary practices and a lack of physical activity [1, 5]. Among Nigerians, there has been a notable shift in dietary habits, with a significant rise in meals consumed outside the home and a growing preference for fast foods high in fat, salt, and sugar [6], leading to a surge in overweight, obesity, and diet-related non-communicable diseases, including hypertension, [6]. Although Nigeria implemented the national nutritional guidelines in 2014 to reduce the risk of hypertension and other NCDs [7], translating these guidelines into actionable advice for clinicians for combating hypertension has been a challenge, possibly because (i) clinicians in Nigeria have not been provided with an effective strategy to provide regionally-specific dietary information to their patients, and (ii) the evidence used to inform Nigeria nutritional recommendations is based on evidence weighted towards non-Nigerian studies which may not be translatable or applicable to manage the contribution of diet towards the rising trend of hypertension risk in Nigeria and other West African countries.

Dietary assessment methods such as diet records and 24-hour dietary recalls can evaluate individual food and nutrient intake [8], but they are time-consuming for clinic use [9]. Alternatively, a brief food frequency questionnaire (FFQ) offers a more convenient approach to assess dietary patterns [9, 10], but effective counselling still requires time and expertise [11], making implementation clinically. To the best of our knowledge, there are no simple dietary assessment tools tailored for clinical practice in Nigeria that are concise without requiring extensive data analysis while still providing personalised dietary support to their patients. Existing comprehensive instruments like food frequency questionnaires (FFQs) and 24-hour recalls [12–14] collect dietary data but require extensive administration and analysis time, limiting their feasibility in busy clinic settings [14]. Similarly, brief screening tools like the Rapid Eating Assessment for Participants (REAP) [15], while efficient, have not been validated in Nigerian unique diet, highlighting the need for region-specific tools attuned to local food culture [16, 17]. The lengthy, Western-based instruments commonly [15–17] often failed to capture Nigerian staple foods like yam, plantain, beans, soups and other local meal [6, 18]. As such, consultation with health professionals and participants in Nigeria is important to ensure that the FFQ is culturally-sensitive and appropriate for clinical practise.

To overcome this gap, the study has set the following objectives: (1) evaluate the acceptability of the FFQ, (2) investigate the feasibility of a dietary assessment tool (FFQ) and its agreement with 24-hour dietary recalls (24HR) in a clinical setting in Nigeria and to develop a scoring system for the FFQ, and (3) test the association between the FFQ score and hypertension risk in Nigeria.

### Study aims and objectives

#### Study aims

The overall aim is to deliver a clinically tested and validated short dietary assessment tool that will be ready to use by clinicians, patients, and researchers across Nigeria to provide personalised dietary advice to patients with hypertension and empower its citizens to improve their diet and take an active role in hypertension prevention.

#### Study objectives

To evaluate the acceptability of the FFQ among the study participants and health professionals.To assess the feasibility of implementing the FFQ in a clinical setting in Nigeria.To examine the agreement between the FFQ and 24-hour dietary recalls in capturing dietary information.To develop a scoring system for the FFQ based on the associations between individual foods and continuous measures of hypertension (Blood pressure).To assess the association between the FFQ score and hypertension.

## Materials and methods

### Study design

This study will adopt a monocentric, retrospective, cross-sectional, controlled, open-label, nonrandomised design with parallel branches that will be conducted in a clinical setting at Rivers State University Teaching Hospital, Port Harcourt, Rivers State, Nigeria. The trial will adhere to the SPIRIT guidelines for effective scheduling and time management of trial participants **(Fig 1).** The study will be conducted in two distinct phases. Phase 1 will investigate the feasibility of the FFQ and its agreement with 24-hour dietary recalls, while Phase 2 will assess the acceptability of the FFQ and validate the association between the FFQ score and hypertension (**Fig 2**).

**Fig 1 pone.0292561.g001:**
[figure not shown]
Schedule of enrolment, interventions, and assessments in accordance with the SPIRIT guidelines. t1: week 1; t2: between week 1and 3, t3: Week 3, t_x_: post-week 3.

**Fig 2 pone.0292561.g002:**
[figure not shown]
Participant selection and sequence of assessments flowchart. FFQ: food frequency questionnaire, 24 HR: 24-hour dietary recalls, BP: Blood pressure, H: Height, W: Weight.

### Participants, interventions and outcomes

#### Study setting

The study will take place at the Family Medicine and Internal Medicine Department outpatient clinics at the Rivers State University Teaching Hospital in Port Harcourt, Nigeria. This clinical setting was chosen due to its accessibility to patients and well-established medical care and research infrastructure.

#### Eligibility criteria

Interested individuals will be screened for eligibility during their regular clinical appointments, where clinicians, nurses, and the research team will use a short questionnaire to evaluate if they meet the inclusion of the study (**Table 1**).

**Table 1 pone.0292561.t001:** Eligibility criteria for the recruitment of study participants (clinical patients).

Inclusion criteria	Exclusion criteria
Age between 18 and 70 years	Individuals < 18 years or > 70 years of age
Men and women	Pregnant women or intent to become pregnant
Hypertensive or non-hypertensive individual	Breastfeeding woman
Individuals resident in Nigeria for the past 2 years.	Diagnosis of other chronic diseases such as cancer, diabetes, renal failure, or endocrine diseases, and previous and recent cardiovascular disease (CVD) and stroke.
Ability to read, write, and communicate over the phone in English	Individuals on dietary restriction or recent changes to their diet or food
Individuals who gave their consent to participate.	Individuals who are currently enrolled in other studies

#### Intervention

*Food frequency questionnaire (FFQ)*. This study will use a 32-question semi-quantitative food frequency questionnaire (FFQ) designed to capture individuals’ usual food intake over the past month for 27 food groups. The list of commonly consumed foods was guided by the Nigerian and Ghana National Nutritional Guideline on Non-Communicable Disease Prevention, Control and Management [7, 19] and supported by our systematic review and meta-analysis regarding dietary factors associated with hypertension in the West African region [5]. The FFQ consists of 26 questions covering major food groups and an additional 6 questions on salt. These food groups encompass a diverse range of foods favourably or unfavourably associated with hypertension, including: fruit, vegetable, fibre-breakfast cereals, rice and pasta, beans, yam and potatoes, fried or fast foods, whole meat, white meat, processed meat, sugary fizzy drinks and fruits, diet non-alcoholic drinks, tea and coffee, soups and stew (fatty soups, vegetable soups, draw soups, native soups, and stews), nuts and seeds, dessert and sweets, fats and oils, salt, milk and milk-based beverages. For each food item, participants will report the frequency of consumption over the past month, with response options ranging from ’rarely or never,’ ’1–2 times/week,’ ’3–5 times/week,’ to ’daily,’ and ’more than once per day. We also acknowledge that the FFQ is likely to evolve as it is tested in more clinics and by more individuals across Nigeria.

#### 24-hour dietary recall (24HR)

A 24-hour dietary recall (24HR) will be used to capture the habitual consumption of foods among the participants [20] and used as the reference method to validate the FFQ. The 24HR will be used to collect dietary information of the participants in the past 24 hours using the multiple-pass method [21, 22].

### Outcomes

*Primary outcome measures*. The primary outcome of this study is to develop and validate a short dietary screening tool (FFQ) for potential implementation in the Nigerian healthcare system for clinical practice, pending the results of this rigorous evaluation. While this tool alone will not eliminate unhealthy diet or hypertension risk, it can help prioritise diet as a practical means of risk assessment and prevention of hypertension in Nigeria if found to be valid, feasible and acceptable. This analysis of the result of the study will focus on descriptive data related to feasibility, validity, reproducibility and qualitative perceptions of the FFQ among the study population. However, limitations exist in the generalizability of the findings beyond Nigeria, as the tool was designed specifically for cultural, lifestyle and dietary habits within this population. Additional research would be needed to adapt and validate the FFQ for other countries and settings. While the study aims to positively impact clinical practice in Nigeria, we acknowledge these limitations upfront and will interpret results accordingly if the FFQ performs well in our evaluations.

*Secondary outcome measures*. Secondary outcomes will evaluate the agreement between FFQ and 24-hour dietary recalls (24HR) in assessing dietary intake, using correlation coefficients to establish consistency between methods. Additionally, we seek to explore the association between FFQ scores and hypertension risk, quantifying the odds ratio that reflects the odds of hypertension about the FFQ scores. Furthermore, we will assess the acceptability of the FFQ through participant-reported feedback, providing insights into the practicality and user-friendliness of the tool.

### Participant timeline

The participant timeline and schedule of enrolment, interventions, assessments, and visits for participants are outlined in **Fig 1** in accordance with SPIRIT guidelines. During Phase 1, a one-month recruitment period will be initiated to identify clinical patients meeting the eligibility criteria. These patients will be approached for informed consent and subsequently categorised into two groups based on their history of hypertension. Participants will undergo comprehensive baseline assessments in the initial week of their clinical appointments. These assessments will encompass the administration of the Food Frequency Questionnaire (FFQ) and the First 24-hour dietary recall (24HR).

The participant’s blood pressure and essential anthropometric measurements, including height and weight, will also be recorded. Moreover, demographic and health status information will be collected to overview the participants’ profiles comprehensively. A second 24-hour dietary recall assessment will be conducted in the subsequent weeks, followed by a final set of assessments in the third-week post-allocation. These final assessments will include the administration of the second FFQ, the third 24-hour dietary recall (24HR), and recording blood pressure, height, and weight measurements.

Phase 2 of the study will involve participants who have provided informed consent. Over four weeks, participants will undergo assessments during their clinical appointments. Central to this phase is the refined FFQ-based dietary intake evaluation, designed to capture detailed information on participants’ dietary habits. Simultaneously, height and weight measurements will be taken to ensure accurate and up-to-date anthropometric data. Additionally, relevant demographic and health status information will continue to be collected, allowing for a comprehensive understanding of participants’ backgrounds and overall health profiles. This phase provides a detailed and in-depth analysis of participants’ dietary habits and their potential correlation with hypertension status.

### Sample size and sampling technique

The targeted sample size for this study was determined by previous studies evaluating the agreement between food frequency questionnaires (FFQs) and 24-hour dietary recalls. These studies have found correlation coefficients (r) ranging from 0.3 to o.7, indicating moderate to strong agreement between the two dietary assessment methods [23–26]. Based on this evidence, a modest correlation coefficient of *r* = 0.5 is considered a good indicator of validity for determining the sample size needed to evaluate the agreement between our clinical FFQ and 24-hour recall [27]. Using G*Power software [28], a priori sample size calculation was conducted for a two-tailed correlation analysis with statistical power = 0.8, alpha = 0.05, and r = 0.5. The analysis indicated that a minimum of 29 participants would be needed to detect a significant correlation between the FFQ and recall measures.

In addition, recent evidence suggests that a sample of approximately 13 participants is sufficient to reach saturation in qualitative studies with a small number of clear objectives (*See Section 3*.*4*.*2*: *Feasibility assessment of FFQ*) [29]. Therefore, the planned sample of 29 participants will be sufficiently powered to evaluate the qualitative evidence and feedback. Nonetheless, to account for an anticipated dropout rate of 20% as well as to accommodate any potential missing/incomplete data, the target sample size will be increased to 50 participants (**Fig 2**) [30, 31]. Furthermore, 25 healthcare professionals consisting of nurses, dietitians, and clinicians at RSUTH will be purposely recruited to provide qualitative feedback on the food frequency questionnaire.

A non-probability convenience sampling method will be used to recruit participants from the outpatient clinics at Rivers State University Teaching Hospital (RSUTH) in Nigeria. Eligible adult patients attending scheduled appointments at the Family Medicine and Internal Medicine Department outpatient clinics will be approached in the waiting areas and invited to participate by the study researcher. Individuals who express interest will be screened for eligibility criteria (**Table 1**). Eligible patients who provide written informed consent will be enrolled until the target sample size of 50 is reached. Additionally, 25 healthcare professionals consisting of nurses, dietitians, and physicians will be recruited through direct outreach and invitation by the researcher from relevant departments at RSUTH. Purposive sampling will be used to select healthcare professionals with expertise in chronic disease management, nutrition counselling, or dietetics.

### Recruitment

The study participants will be adult clinical patients and will be recruited from the Rivers State University Teaching Hospital (RSUTH) outpatient clinics in Port Harcourt, Rivers State, Nigeria. The recruitment methods for phases 1 and 2 of this study will involve a multifaceted approach. Participants (clinical patients) will be recruited through recruitment posters displayed in key hospital areas, clinician referrals, and engaging discussions during morning briefing sessions where vital signs are taken from clinical patients in internal medicine and family medicine departments. The healthcare professionals will identify eligible participants based on study criteria, and informational posters will provide essential study details and refer interested participants to the study team for further screening.

### Assignment of interventions

Participants in this study will be allocated into non-hypertensive and hypertensive groups based on their history of hypertension, as illustrated in **Fig 2**. Allocation will be conducted following predefined criteria and without randomisation. The implementation of group allocation will be carried out by the primary investigator based on the predetermined criteria. Participants will not be informed of their assigned group during their respective clinic appointments. Allocation will be conducted in a standardised and systematic manner to uphold the integrity of the study.

### Data collection, management, and analysis

#### Data collection

*Phase 1*. ***Feasibility assessment of FFQ*.** The feasibility of the FFQ will be evaluated in a small number of participants (n = 75) in a ratio of 2:1 consisting of 50 clinical patients and 25 healthcare professionals to ensure adequate saturation in both groups (**Fig 1**). In the feasibility assessment, eligible clinical patients and healthcare professionals will fill out the questionnaire and be asked to provide feedback on the clarity, ease of use, cultural appropriateness and difficulty encountered in answering the questions. Additionally, the healthcare professionals will provide feedback on the clinical relevance and potential impact on patient care and suggest improvements to optimise the questionnaire’s effectiveness. In summary, we will be well-powered to evaluate feasibility from the perspective of patients and clinicians.

#### Validation and reproducibility of the FFQ

The FFQ will be administered to clinical patients (*n* = 50) twice (i.e., first and third visits) to quantify the intake of food items. Additionally, an inconsecutive three (3) repeated 24HR, including two weekdays and one weekend day, will be used to collect dietary information from the clinical patients for the past 24 hours using the multiple-pass method [21, 22] at the time of visits and intervals between the two FFQs administrations (**Fig 1**). The reproducibility of the FFQ will be assessed by measuring the level of agreement between the two administrations of the FFQ. Furthermore, the validation will be assessed by evaluating the agreement level between the FFQ and the average of the three 24-hour recalls [32, 33]. Healthcare professionals are not involved in the patient FFQ validation stage.

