### Statistical analysis

Statistical analyses will be conducted using R programming language version 4.3.0 [35] with significance level set at p<0.05. Descriptive statistics will be used to analyse categorical and continuous variables. Categorical demographic variables will be analysed using frequency distribution, while continuous demographic variables will be summarised as mean and standard deviation for normally distributed variables and median and interquartile range (IQR) for non-normally distributed variables. As the frequencies of food groups are not normally distributed, differences in frequencies between the two FFQs (FFQ1 vs. FFQ2) and between the two methods (24 HR vs. FFQ2) in phase 1 will be tested using Wilcoxon’s signed-rank test.

Feasibility and acceptability will be assessed through descriptive analyses, including means and 95% confidence intervals (CI), qualitative feedback, and content analysis of indicators related to the process (e.g., proportion interested, started, completed FFQ) and resource (e.g., time to complete and review, rated performance, and practicality).

The West African Food Composition Table will be used to calculate the nutrient content (macronutrients such as energy, carbohydrates or sugar, proteins, fats, and fibre and minerals such as sodium and potassium) of the foods reported in both the FFQ and 24HR. The mean and distribution of nutrient intakes obtained from the FFQ and 24HR will be calculated, and a comparison will be made to assess the differences using the Wilcoxon signed-rank test. Pearson correlations will be used to calculate the correlation coefficients between the FFQ and 24HR for each nutrient to assess the agreement between the FFQs and 24HR and the reproducibility of the FFQs. Additionally, the agreement between the FFQ and the average of three 24-hour dietary recalls will be estimated using Intraclass Correlation Coefficient (ICC), de-attenuation of the correlation coefficients, or quintile cross-classification analysis and the Bland-Altman plots will be used to visualise the agreement between the recalls and FFQ [36–38].

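### Averaging two weekday recalls and one weekend recall gives weekends a weight of 1/3 instead of 2/7, which slightly shifts the reference in the level comparisons

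*Protocol article*

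**What the plan says.** The section on validation and reproducibility plans for each clinical patient "inconsecutive three (3) repeated 24HR, including two weekdays and one weekend day". It then states that "the validation will be assessed by evaluating the agreement level between the FFQ and the average of the three 24-hour recalls". The Statistical analysis section repeats the estimator: "the agreement between the FFQ and the average of three 24-hour dietary recalls will be estimated" by ICC, de-attenuated correlations or quintile cross-classification, with Bland-Altman plots.

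The same section compares levels. Food-group frequencies from 24HR and FFQ2 are tested with Wilcoxon's signed-rank test. For nutrient intakes from FFQ and 24HR, "a comparison will be made to assess the differences using the Wilcoxon signed-rank test".

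The target is stated for both instruments. The FFQ is "designed to capture individuals’ usual food intake over the past month for 27 food groups" (Intervention). The recall "will be used to capture the habitual consumption of foods among the participants" and is the reference method (24-hour dietary recall). No section mentions day-of-week weights.

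**The concern.** The day mix and the estimator are both written down, and together they do not quite return the stated target. Over a month, a two-day weekend supplies 2/7 of the days, but the average of three recalls gives the weekend day 1/3. Even with error-free recalls, the reference then lies above usual intake for items eaten more at weekends, and below it for items eaten less.

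For an item that the sample as a whole eats more at weekends, the shift has the same sign on average, so recruiting more patients does not remove it. A comparison of levels would read it as bias of the FFQ. At stake is the interpretation of the Wilcoxon results and of the Bland-Altman mean difference for such items.

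**Working it through.** **The plan's own figure.** Sample size and sampling technique gives a minimum of 29 for r = 0.5, two-sided alpha 0.05 and power 0.80. By Fisher's z, ((1.960 + 0.842)/0.549)² + 3 = 29.01. Simulated power is 0.798 at n = 28 and 0.814 at n = 29. The figure of 29 is reproduced, and nothing below changes it or the target of 50.

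**Inputs.** From the article: two weekday recalls, one weekend recall and their average. Assumed: a two-day weekend, which the article does not define, and R, the ratio of weekend to weekday intake, which the article does not give.

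**Weights.** Weekend weight in the equal-weight mean: 1/3 = 33.3%. Calendar share: 2/7 = 28.6%. Gap: 1/3 − 2/7 = 1/21 = 4.76 percentage points. The reference is shifted by 1/21 of (weekend − weekday intake).

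**Relative size.** With weekday intake w, the equal-weight mean is w(2 + R)/3 and the calendar mean is w(5 + 2R)/7. Their ratio is 7(2 + R)/[3(5 + 2R)].

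| R (assumed) | Ratio | Shift |
|---|---|---|
| 1.1 | 21.7/21.6 | +0.46% |
| 1.2 | 22.4/22.2 | +0.90% |
| 1.5 | 24.5/24.0 | +2.08% |
| 2 | 28/27 | +3.70% |

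**Correlations.** A shift common to all patients leaves Pearson's r and the quintile ranks unchanged. If the weekend effect varies between people (between-person SD 1, day-to-day SD 1 to 2, SD of the weekend effect 0.2 to 1.0, all assumed), the correlation of the reference with true usual intake differs by 0.001 to 0.006 between the two weightings. The equal-weight mean is marginally the higher.

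**Wilcoxon error rate.** Lognormal simulations used an unbiased FFQ, n = 50 and a nominal 5% level.
- Day-to-day log SD 0.3 to 0.5, FFQ error SD 0.2 to 0.4: the equal-weight reference rejects in about 7–10% of trials at R = 1.5, 10–16% at R = 2 and 13–27% at R = 3. The 5:2 weighted reference stays at about 4–6.5%.
- Day-to-day SD 0.8, FFQ SD 0.5: the equal-weight reference rejects 4.1%, 4.3% and 5.2% at R = 1.5, 2 and 3. The weighted reference rejects 4.9–6.1%.
- SDs 1.0 and 0.6: 4.8–5.3% for equal weights, against 5.8–6.4% weighted.

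The inflation therefore depends on low assumed noise. The shift in the mean does not.

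**Variance of the weighted mean.** Equal weights: 3 × (1/3)² = 0.3333. Weighted: 2 × (5/14)² + (2/7)² = 0.3367, a rise of about 1%.

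**The case against.** The article says average, not unweighted average. Equal weights are an inference, and an article may leave day weights to a fuller document. The inference is nevertheless the ordinary reading: the term appears in two sections, next to a fixed day mix, with no hint of weights.

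The measures that size and judge the study are barely touched. Secondary outcome measures defines agreement through correlation coefficients, the sample size rests on r = 0.5, and the Discussion looks for strong ICC values and correlations above 0.4. No pass or fail rule hangs on the Wilcoxon tests or the Bland-Altman plots. This stands, and it confines the point to the level comparisons.

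With three recalls, 2:1 is the closest whole-number split to 5:2. This also stands. It defends the choice of days, which is not in question; weighting closes the remaining gap without changing the recalls.

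A reader might infer that a food eaten only at weekends shows the rule failing: twice a week in truth, 7 × 1/3 = 2.33 a week in the reference, outside the FFQ category that ends at 2. That proves little. With 5:2 weights, a food reported in one weekday recall only scores 7 × 5/14 = 2.5 a week, which also falls between categories. The cause is the coarseness of three recalls, not the weighting.

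**Conclusion.** The point holds in a limited form and is minor. On the ordinary reading of the text, the reference mean is off by 1/21 of the weekend-weekday difference: under 1% of intake if weekends are 20% higher, and 3.7% if weekend intake doubles. This rests on a two-day weekend and on assumed ratios. The shift reaches the Wilcoxon comparisons of FFQ with 24HR, the Bland-Altman mean difference and, slightly, an ICC for absolute agreement.

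Two stronger readings are not supported. One is that the validation as a whole is compromised: correlations, cross-classification and the sample size are essentially unaffected. The other is that an unbiased FFQ would often be declared biased: those rates need large weekend ratios and low day-to-day variation together, and the article gives neither.

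**What to change.** In Validation and reproducibility of the FFQ and in Statistical analysis, define the reference for the level comparisons as (5 × mean of the weekday recalls + 2 × weekend recall)/7 when both day types are available. For consistency, use the same reference in the other agreement analyses. When the weekend recall is missing, use the plain mean of the available recalls and flag it as such, because that value carries no weekend information. Fix the rule before the data are analysed.

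The cost is one definition and a fallback rule. The fallback is needed because the article itself expects 20% dropout and some incomplete data. No extra data are required, since the day of the week is already part of the recall design. The variance factor rises from 0.3333 to 0.3367.
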